## **Methods**

**Study design:** The proposed project is a prospective, single blind, randomized controlled intervention trial in patients with chronic stroke.

**Setting:** Patients will be recruited from the Rehabilitation Center Paramaribo; from the community and from the union for people after stroke.

**Patient population:** Patients with chronic ischemic stroke and following the inclusion criteria can be included in the study:

Inclusion criteria:

- ability to give informed consent
- ability to understand measurement procedures defined as MMSE >24 [22]
- last stroke >6 months ago
  
- mild to moderate stroke deficit defined by Fugl Meyer test score of 27 to 90 for upper and lower extremities [12]
- FAC  $\geq 3$
- medical clearance to participate in a moderate exercise program
- living at home and having a minimum of 5 stairs at home

Exclusion criteria:

- serious cardiac condition [22]
- other serious end organ damage
- other neurological deficits leading to disability
- uncontrolled blood pressure (systolic pressure >140, diastolic pressure >90) [22]

**Statistical power and sample size:** Sample size calculation was performed with PS Power and Sample Size Calculation (<http://biostat.mc.vanderbilt.edu/PowerSampleSize>) The sample size for the two-sample case (training versus control) was estimated on the basis of the results of Moore et al [13] for effect of exercise on cardiorespiratory capacity. In this study the response for peak VO2 within each subject group was normally distributed with standard deviation 3.4. If the true difference in the experimental and control means is 3.0, we will need to study 17 experimental subjects and 17 control subjects to be able to reject the null hypothesis that the

population means of the experimental and control groups are equal with probability (power) 0.8. The Type I error probability associated with this test of this null hypothesis is 0.05. We chose to aim for a sample size of 20 patients per group taking drop outs into account.

Participant stratification will be balanced for gender because men tend to have higher aerobic capacity and muscle strength than women. The participants will be assigned randomly to a group by a computer program ([www.randomization.com](http://www.randomization.com)). Informed consent (appendix I) must be signed by every participant.

**Intervention** There is an intervention group (physical fitness exercise) and a control group (usual care) [13].

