The intervention will be provided by a physical therapist for 4 weeks (3 times/wk, 70 minutes). This duration of intervention was selected because it improved the cardiorespiratory function of chronic stroke survivors [11]. After that a telephone supervised method for 4 weeks is done to monitor if the patient is continuing the exercise program at a given intensity. To progress in cardiorespiratory fitness level a pedometer based step goal [4] will be set.

**Measurements:** Following measurements and paper and pencil surveys will be undertaken in order to evaluate the subjects at baseline at 4 weeks, 8 weeks and 5 months:

**Anthropometric characteristics** weight, height, body mass index, % fat (bio-electrical impedance) and waist and hip circumference will be measured.

**Exercise tolerance** (peak VO2) will be assessed by submaximal graded cardiopulmonary exercise testing (CPET) with breath-by-breath analysis (Jaeger Oxycon Mobile®) on a cycle ergometer. Submaximal fitness parameters will include 1st and 2nd ventilatory thresholds, oxygen uptake efficiency slope and the VE/VCO2-slope. We will use a graded protocol in which the patient starts with a 10 min warming-up session at zero workload [12] followed by workload increments of 10W every minute until maximal effort is reached or symptoms appear [3, 12]. Submaximal effort is defined as the inability to continue cycling at a pace of 50-60 revolutions per minute due to shortness of breath and/or leg fatigue.

**Hemodynamic and vascular function at rest** will be non-invasively assessed by means of the Nexfin device which will provide resting systolic and diastolic blood pressure, cardiac output, stroke volume and systemic vascular resistance. Furthermore brachial ankle index will be determined by blood pressure measurements at non-paretic upper arm and ankle. Finally arterial stiffness will be evaluated by use of the Arteriograph.

**Lung function** will be evaluated by vital capacity and forced expiratory volume in 1 second measured before starting the CPET, using the same equipment for breath by breath analysis.

**Habitual physical activity** will be objectively assessed during 7 consecutive days and nights by means of the physical activity device that will also be used to guide the intervention, designed to be worn constantly around the upper arm (like a watch) [23].

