**Walking endurance** will be tested with the 6-minute walk test. This test is a reliable submaximal test of cardiorespiratory capacity in people with stroke [24, 25].

**Quality of gait** will be defined by spatiotemporal parameters such as step length, stride length, step width, paretic stance time and gait speed. These parameters will be recorded in a human movement laboratory by two camera's (Panasonic HDC-TM900 3 MOS HD camcorder and Canon powershot SX40 HS) which capture data that will be analyzed with Kinovea, an open source video tool.

**The manual muscle testing (hand-held dynamometer), and handgrip strength test** will be used to evaluate upper limb function [26-29] and knee extensor strength [30, 31].

**Balance** will be evaluated by the Berg balance scale, which consists of 14 tasks and a score range of 0-56 [32].

**Health related quality of life** will be evaluated using the SF-12 questionnaire [33-35].

**Disabilities of arm, shoulder and hand** will be evaluated by means of the DASH questionnaire [36, 37].

**Exercise self-efficacy** will be evaluated by use of the Dutch translation of the Exercise Self-Efficacy Scale (ESES) [38].

**Database management** will be performed by use of Microsoft Excel 10.0. All data will be anonymized before being processed. Repeated measures ANOVA will be performed by use of SPSS statistical software in order to reveal differences between control and intervention groups regarding the primary and secondary outcome measures.

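### Repeated measures ANOVA over baseline and three follow-up visits makes less use of the data than a baseline-adjusted mixed model, and the power it gives up grows if visits are missed

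*Protocol*

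**What the plan says.** The analysis text stands at the end of Methods, under Database management: "Repeated measures ANOVA will be performed by use of SPSS statistical software in order to reveal differences between control and intervention groups". It applies to the primary and secondary outcomes alike. No covariate, contrast, visit or missing-data rule accompanies it.

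Under Measurements, the visits are set so as to "evaluate the subjects at baseline at 4 weeks, 8 weeks and 5 months". Baseline is thus one of four occasions, and no change score or baseline adjustment is mentioned.

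The sample-size paragraph takes peak VO2 as "normally distributed with standard deviation 3.4" and a true difference of 3.0, arrives at "17 experimental subjects and 17 control subjects", and adds: "We chose to aim for a sample size of 20 patients per group taking drop outs into account". The same paragraph says that allocation is balanced for gender.

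The Objectives ask for short-term and longer-term effects of an 8-week programme on aerobic capacity, gait quality and health-related quality of life.

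**The concern.** This is about a method that the protocol fixes, not about detail left to an analysis plan. A plan consistent with the protocol would inherit repeated measures ANOVA. Three features of it fit this trial poorly.

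- **Baseline.** With baseline as a level of time, the treatment effect at a visit is judged as a change from baseline. Subtracting the whole baseline value adds noise unless the correlation between visits is high. Using baseline as a covariate removes only the part that predicts the outcome.
- **Missing visits.** The classical SPSS repeated-measures procedure uses complete cases. A patient seen at 8 weeks but not at 5 months contributes nothing, even to the 8-week question.
- **Question answered.** The group-by-time test has 3 degrees of freedom and asks whether the profiles differ anywhere. It does not by itself separate an early effect from a lasting one.

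At stake are precision in a trial of 40 patients and, if attendance relates to outcome, the soundness of a comparison limited to completers.

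**Working it through.** **Inputs from the protocol:** SD 3.4; difference 3.0; alpha 0.05 (taken as two-sided, as the protocol does not say); 20 per group; four visits.

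**Assumed, because the protocol gives no figure:** equal variances and equal correlation r between visits (compound symmetry), r from 0.5 to 0.8; the full difference of 3.0 at 8 weeks; either complete data or 10% missing at each follow-up visit, independently and at random.

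**The plan's own figure.** For a two-sample t-test the noncentrality is (n/2) × 3.0² / 3.4². With n = 17 this is 8.5 × 9 / 11.56 = 6.62 on 32 df, power 0.70. With n = 20 it is 7.79 on 38 df, power 0.78. The stated 0.80 with 17 per group is therefore not reproduced two-sided. That is a separate matter; here it shows only that there is little power to spare.

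**Step 1: 8-week-minus-baseline contrast from the ANOVA, complete data.** The variance of a change is 2 × 3.4² × (1 − r), and the noncentrality is (20/2) × 9 divided by that variance.

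- r = 0.5: variance 11.56, noncentrality 7.79
- r = 0.7: variance 6.94, noncentrality 12.98
- r = 0.8: variance 4.62, noncentrality 19.46

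**Step 2: baseline-adjusted 8-week comparison, complete data.** The residual variance is 3.4² × (1 − r²). The test has 40 − 3 = 37 df; gender is left out of this calculation.

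- r = 0.5: variance 8.67, noncentrality 10.38
- r = 0.7: variance 5.90, noncentrality 15.27
- r = 0.8: variance 4.16, noncentrality 21.63

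The ratio of the two variances is 2(1 − r)/(1 − r²) = 2/(1 + r): 1.33, 1.18 and 1.11. This is why the gain shrinks as r rises.

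**Step 3: 10% missing per follow-up visit.** Complete cases number 40 × 0.9³ = 29.2. The ANOVA noncentrality falls by the factor 0.9³ = 0.729; at r = 0.5 it becomes 5.68. The mixed model keeps every observed follow-up value. Averaging its information over the missing-visit patterns gives a noncentrality of 9.49 at r = 0.5.

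**Power at 8 weeks, 20 randomised per group** (ANOVA: contrast's own error term, with the pooled error term in brackets):

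| r | Missing per visit | ANOVA contrast | Baseline-adjusted |
|---|---|---|---|
| 0.5 | 0% | 0.78 (0.79) | 0.88 |
| 0.7 | 0% | 0.94 (0.95) | 0.97 |
| 0.8 | 0% | 0.99 (0.99) | 0.99 |
| 0.5 | 10% | 0.63 (0.65) | 0.85 |
| 0.7 | 10% | 0.84 (0.86) | 0.95 |
| 0.8 | 10% | 0.95 (0.96) | 0.99 |

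**Step 4: the omnibus test.** With a constant effect of 3.0 at all three follow-up visits, r = 0.5 and complete data, the group-by-time test has power 0.81. The joint 3-df test of the mixed model has 0.94. With 10% missing per visit the figures are 0.66 and 0.93.

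**The case against.** The protocol spends one sentence on the analysis. It does not state that baseline is a level of the time factor, nor that incomplete patients are excluded. The first is the ordinary reading of a four-visit list with no covariate; the second is how the classical SPSS procedure behaves. Neither is a written rule, and this part of the objection stands.

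Several stronger readings are tempting, and the protocol does not support them:

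- *The ANOVA yields no estimate at any visit.* Contrasts can be obtained from the same model, and naming them may be left to an analysis plan.
- *The Objectives name 8 weeks and 5 months as the time points.* They name none; 8 weeks appears there as the length of the programme. Matching short and longer term to those two visits is a sensible reading, not the protocol's wording.
- *A constant effect of 3.0 is diluted to (0 + 3 + 3 + 3)/4 = 2.25.* This is true of the group main effect, but nothing in the protocol selects that term, and group-by-time is the more natural test.
- *The analysis departs from the two-sample comparison behind the sample size.* So would a mixed model, so this does not favour either.
- *Missed visits remove about a quarter of the patients.* 1 − 0.9³ = 27% assumes independent, intermittent gaps. Going from 20 to 17 per group is a 15% allowance. If those patients leave for good before any follow-up, both methods lose the same people. At 17 per group and r = 0.5 the noncentralities are then 6.62 and 8.5 × 9 / 8.67 = 8.82, giving power of 0.70 against 0.82. In that case the gap comes from baseline adjustment alone.

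It is also fair that with complete data and high correlation the two approaches nearly tie. For an effect at 8 weeks only and r = 0.7, group-by-time reaches 0.97, and so does the adjusted 8-week comparison.

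**Conclusion.** The concern holds as a matter of efficiency and fit. The protocol commits to a method for which a better one exists on the same data and in the same software. Comparing 8-week tests like for like, complete data cost about 10 percentage points of power at correlation 0.5, about 3 at 0.7 and almost none at 0.8. With 10% missing per follow-up visit the cost is about 20 points at correlation 0.5 and about 10 at 0.7.

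These sizes rest on compound symmetry, the protocol's SD and difference, and assumed correlations and missingness. The direction at 8 weeks does not depend on the exact values: under equal correlation the adjusted variance never exceeds the change variance, and using partial data cannot leave fewer patients. Bias from selective drop-out is possible under the complete-case procedure, but nothing in the protocol shows that it will occur.

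**What to change.** Replace the ANOVA sentence with a linear mixed model in SPSS on the 4-week, 8-week and 5-month values of each outcome. Fixed effects: group, visit, group-by-visit, the baseline value of that outcome, and gender (the stratification factor). Allow for correlation between a patient's visits, and include all randomised patients with at least one follow-up value. Report the adjusted group difference with its 95% confidence interval at 8 weeks and at 5 months.

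Whether one outcome at one visit should be the sole confirmatory test is a separate decision for the sponsor; this change does not require it.

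Cost: one paragraph of wording and a little more analysis work, with no new patients, visits or measurements. With missing data, validity rests on the missing-at-random assumption, which should be stated.

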### Time Planning:

Start research project: March 1st 2016

Anticipated end of research project: March 31th 2017

**There will be no charges for the patient and there will also be no extra costs for the rehabilitation center as all measurements will be performed by staff and equipment belonging to the research group.**

